# Study regulations

## Information and consent

Patients are recruited according to the inclusion criteria and informed consent is obtained at least 24 hours before inclusion in the study. Age-appropriate consent forms are available. In case of age <18 years, parents and child are consented in accordance.

## Description of the procedures

Potential study participants are screened on an interdisciplinary basis according to the inclusion criteria through the participating centers. The screening includes laboratory analysis and pre-interventional imaging with US/CT/MRI to confirm the diagnosis and to identify possible treatment options, which are performed with the routine clinical workup. Furthermore, the exact size assessment of the initial extent of the vascular malformation (volumetric measurements, flow characteristics) is being performed based on the cross-sectional imaging data.

After detailed study information (orally and written) and informed consent, the patient is included in the study. The pre-therapeutic assessment is composed of the same subjective (SF-36v2/SF-10, VAS, Likert scale of severity of symptoms) and objective (general appearance and location-specific signs) surveys that are done during the follow-up appointments. Following interdisciplinary consensus, multimodal treatment is initiated

**Compression treatment** is considered as the baseline therapy for all vascular malformations. Patients are supplied with custom made compression garments (class II). Depending on severity of disease, permanent compression therapy may be applied or temporary compression may be considered sufficient.

**Embolization** is performed under general anesthesia following standard operating procedures. Access to the lesion will either be gained via a transarterial, transvenous or percutaneous route, or a combination of the latter. For transarterial or transvenous access is gained via a femoral or brachial access using a 5-8 French-sized catheter equipment. If additional percutaneous access is required lesion will be punctured under ultrasound guidance using a 20-21G needle. After contrast injection digital subtraction angiograms are acquired and subsequently embolization is performed under fluoroscopy guidance. Periprocedural anticoagulation is performed using unfractionated heparin in a weight-adapted manner. Periprocedural antibiosis is not applied routinely. Depending on the extent and morphology of the lesion multiple treatment sessions will be required in order to achieve complete/near-complete embolization. All agents used for embolization purposes are CE-marked.

In case of **surgical resections** of AVM tissue, surgery is performed after complete/near-complete embolization. Surgical resection is similarly performed under general anesthesia. Neuromonitoring will be routinely used in case of proximity of the AVM to major nerve structures. Surgical resection is limited to mass-forming AVM tissue, complete resection of the entire malformation is rarely possible and not goal of the procedure.

Peripheral venous blood samples will be obtained on the day before, on day 1 and 3 following embolization as well during follow up at the same time points of health related QoL assessment. Blood samples will be processes and subsequently frozen until subsequent biomarker analysis.

# Follow-up

Follow-up will be performed following a dedicated time line:

- In case of conservative therapy biannually for 36 months
- Before initiation of interventional therapy as well as before each cycle of interventional treatment
- After initiation of interventional therapy every 6 months
- After completion of interventional therapy follow-up is performed at 6 (primary endpoint), 12 , 24 and 36 months

A flowchart with the corresponding clinical, laboratory and radiological examinations is attached at page 24.

# Adverse events (AE) / serious adverse events (SAE)

Adverse events are considered to be directly or indirectly related to the study protocol. A serious adverse event is considered to be a study-related AE that:

· leads to death.

· is life-threatening (the danger to life must have actually existed; it is not enough that the event could have led to death if it would have been more serious).

· requires hospitalization or prolongs a hospital stay.

· leads to a permanent and significant disability.

The invasive therapy regimens as listed above can cause a variety of side effects and procedure related complications. As those events are however not related to the observational character of the study protocol, those are not considered to be Adverse Events (AE) or Serious Adverse Events (SAE).

Procedure-related events, not considered to be AE/SAE:

· Bleeding up to hypovolemic shock with indication for blood transfusion or emergency intervention/surgery

· Infections with consecutive systemic spread up to sepsis/shock including septic arthritis

· Damage caused by ionizing radiation (especially radiation dermatitis)

· Unforeseen Injury to tissue adjacent to the AVM, especially soft tissue, skin, vessels and nerves

· Unforeseen cardiovascular disorders such as pulmonary embolism and stroke

· Contrast medium or drug-induced renal failure, which may require dialysis treatment

· Contrast medium-induced thyroid disorders

· Allergic reactions

# Statistics

Analysis of clinical patient data, QoL data and Biomarkeranalysis will be performed separated from each other in a blinded setting. The study has an exploratory focus. All statistical testing will be performed based on a significance level of α=5%. No adjustment for multiple testing is planned.

Standard descriptive statistics will be used when reporting the study data. For continuous data, distribution parameters (mean, standard deviation, minimum, median, and maximum) will be computed and for categorical data, frequency counts will be given. If needed, 95% confidence intervals will be specified.

For the primary study parameters (scores PCS and MCS from adult SF-36v2 quality of life questionnaires, as well as PHS and PSS from kids SF-10 questionnaires), paired t-tests will be calculated comparing the scores at baseline to the respective scores at 6 months after the end of treatment (for embolized patients) or at the 24 months FU (for patients with conservative or medical treatment).

All QoL scores and subscores, as well as patient and physician reported pain and symptom data will be tabulated by study visit. Where appropriate, such data will also be summarized for different patient subgroups (e.g., age group, Schobinger stage, study treatment, etc.)

Morbidity, Mortality, and recurrence rates will be compared for different patient subgroups using Chi Square or Fisher’s exact test.

Summary statistics for AVM nidus volume reduction will be presented stratified by clinical outcome, as well as by patient subgroups, as needed. Crosstabulations of AVM devascularization (100% / 76-99% /50-75% / < 50% devascularization) vs. different clinical outcomes will be presented.

A sample size of N=74 (for children and adults, respectively) achieves 80% power to detect a mean of paired differences of 5 with an estimated standard deviation of differences of 15 and with a significance level (alpha) of 0,05 using a two-sided paired t-test.

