# Study objectives

The study objective is to determine the effectiveness, safety and clinical outcome including health-related Quality of Life of multimodal treatment of arteriovenous malformations. Therapy options include conservative management, medical treatment, minimally-invasive image-guided therapy (sclerotherapy, embolization) and surgery as well as combinations of all of the above. Of note, especially image-guided therapy routinely requires multiple therapy sessions. Clinical outcome shall therefore be assessed before initiation of treatment, during therapy (including in between multiple therapy sessions) as well as at defined time points after therapy of the AV malformation. Therapy assessment is based on the recommendations of the international core outcome set (OVAMA)^17^. Additionally, liquid biopsies are being obtained from peripheral blood to investigate potential biomarkers (cytokines, chemokines, growth factors) for therapy response or/and disease progression.

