## Secondary study objectives

To determine effectiveness and clinical outcome of multimodal treatment of vascular malformations the following points are additionally examined as secondary study objectives (based on OVAMA^17-20^):

- *Physician-reported* signs: general appearance (for example swelling, pulsation, ulceration, cardiovascular health issues, bleeding) and location-specific signs (for example extremity length discrepancy, physical impairment)
- Imaging Response: MR-angiographically measured reduction of the size (volume) of the nidus of the AVM and degree of devascularization, in case of superficial cutaneous lesions patient photographs will be considered additionally
- Concordance between clinical and imaging outcome
- Serum/Plasma levels and respectively change of levels of potential biomarkers for prediction of therapy response or/and disease progression in an exploratory manner
- Recurrence Rate following multimodal AVM treatment
- Other local and systemic side effects at the follow-up visit

Assessments of the points listed above will be conducted at the following time points:

- At time of first presentation to the vascular malformation clinic after inclusion in the study
- In case of conservative management biannually thereafter for 36 months
- Before initiation of interventional/surgical therapy as well as before each cycle of l treatment
- After initiation of interventional/surgical therapy every 6 months
- After completion of interventional/surgical therapy follow-up is performed at 6 (primary endpoint), 12, 24 and 36 months

To determine safety of multimodal treatment of vascular malformations the following points are additionally examined as secondary study objectives:

• Treatment-associated morbidity including temporary (e.g. vascular procedure complication requiring surgical management, local tissue necrosis, infection, bleeding, thrombosis, embolism due to unintended dislocation of the agent to the lung, cardiovascular systemic complications) and permanent sequalae (e. g. motoric and sensory nerve injury, lasting joint movement restrictions) and mortality

• Other acute local and systemic side effects peri- and postinterventional

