## Primary Endpoint:

*Patient-reported* health-related Quality of Life in a multimodal therapy concept for AV malformation treatment at 6 months after completion of invasive treatment. In order to investigate the QoL in a standardized way, established questionnaires (SF-36v2, SF-10) will be used.

- Adults: SF-36 Version 2: The SF-36v2 for adults (> 13 years) consists of eight scaled scores, which are the weighted sums of the questions in their section. The eight sections are vitality (VT; feeling energetic, absence of fatigue), physical functioning (PF; extent to which health limits daily physical activities), bodily pain (BP; intensity of pain and effect on activities), general health perception (GH; current health status, health expectations and resistance to illness), physical role functioning (RF; extent to which physical health interfere with typical role functions), emotional role functioning (RE; extent to which emotional health interferes with typical role functions), social functioning (SF; extent to which health-related problems interfere with normal social activities) and mental health (MH; general mental health, including anxiety, depression, positive affects). These eight sections yield two summary measures:
  - physical component summary (PCS)
  - mental component summary (MCS).
- Kids: SF-10: The SF-10 is a 10-item questionnaire for children aged 5 – 13 years designed to measure health-related QoL in children. Unlike the SF-36v2 it should be completed by caregivers. The scoring method yields two summary measures:
  - physical summary score (PHS-10)
  - psychosocial summary score (PSS-10)

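### The primary endpoint is set 6 months after invasive treatment, but the primary tests also take conservative and medical patients at 24 months, and the stated 80% power holds for the defined endpoint only if nearly every patient is treated invasively

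*Protocol*

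**What the plan says.** - **Endpoint.** Protocol, Primary Endpoint: quality of life under a multimodal concept for "AV malformation treatment at 6 months after completion of invasive treatment". The measures are the SF-36v2 and SF-10 summary scores.
- **Visit schedule.** Protocol, Follow-up: "After completion of interventional therapy follow-up is performed at 6 (primary endpoint), 12 , 24 and 36 months". Secondary study objectives attaches the same label to a slightly wider event: "After completion of interventional/surgical therapy follow-up is performed at 6 (primary endpoint". Conservative patients have their own line in Follow-up, "In case of conservative therapy biannually for 36 months", with no visit marked as primary.
- **Primary test.** Protocol, Statistics: paired t-tests on the primary study parameters compare baseline with the score "at 6 months after the end of treatment (for embolized patients) or at the 24 months FU (for patients with conservative or medical treatment". No other section names 24 months as a primary time point.
- **Scope of the study.** Protocol, Study objectives: "Therapy options include conservative management, medical treatment, minimally-invasive image-guided therapy", followed by surgery and combinations.
- **Sample size.** Protocol, Statistics: "A sample size of N=74 (for children and adults, respectively) achieves 80% power to detect a mean of paired differences of 5", with an SD of differences of 15 and two-sided alpha of 0.05. Study population gives 148 patients in total.

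**The concern.** The protocol fixes both the endpoint and the test, and they do not match. The endpoint covers only patients who have had invasive treatment, counted from its completion. The test also admits patients who have had none, at a later visit and on a different clock. A later analysis plan could not settle this without overriding one of the two sections.

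Two things are at stake. First, the primary result is not unique. One analyst could pool the two groups, a second could test them separately, and a third could keep only the patients whom the endpoint section covers. All three could cite the protocol. A pooled mean change would also depend on the treatment mix that happens to be recruited. Second, the 74 per age group is a count of all patients, so any who are managed conservatively reduce the number available for the endpoint as defined.

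**Working it through.** **Inputs from the protocol.** Mean paired difference 5, SD of differences 15, two-sided alpha 0.05, 74 per age group (Statistics). Total 148 = 2 × 74 (Study population), so there is no reserve.

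**Inputs assumed.** The protocol gives neither the share of conservative or medical patients nor their expected change. I take shares of about 10%, 20% and 30% (7, 15 and 22 of 74) and mean changes of 0, 2.5 and 5, with a within-group SD of 15 throughout.

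**Formula.** Exact power of the paired t-test from the noncentral t distribution, with df = n − 1 and noncentrality (difference / SD) × √n.

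**Step 1: the plan's own figure.** For n = 74, noncentrality = (5/15) × √74 = 2.867 and power is 80.8%. For n = 73 it is 80.2%, and for n = 72 it is 79.7%. The stated figure reproduces, and 73 is the smallest n that reaches 80%. Once two of the 74 in an age group fall outside the defined endpoint, its power is below 80%.

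**Step 2: test limited to invasively treated patients.** The last column is 74 / (1 − share), rounded up.

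| Conservative share | Invasive n of 74 | Power | Enrolment per age group to keep 74 invasive (total) |
|---|---|---|---|
| 10% | 67 | 76.7% | 83 (166) |
| 20% | 59 | 71.2% | 93 (186) |
| 30% | 52 | 65.5% | 106 (212) |

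If the conservative group is tested on its own, n is 7, 15 or 22. Power is then 11.6%, 22.5% or 32.0%, even at a true change of 5.

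**Step 3: pooled test with all 74.** With conservative fraction f and conservative mean change d, the pooled mean is 5(1 − f) + d·f and the pooled variance is 15² + f(1 − f)(5 − d)². For example, with f = 15/74 and d = 0, the mean is 3.99, the SD is 15.13 and power is 60.9%.

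| Conservative share | d = 0 | d = 2.5 | d = 5 |
|---|---|---|---|
| 10% | 72.2% | 76.8% | 80.8% |
| 20% | 60.9% | 71.8% | 80.8% |
| 30% | 50.2% | 67.1% | 80.8% |

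Pooling costs power only if conservative patients change by less than 5 or vary more than assumed.

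**The case against.** The best defence is that Statistics follows the study's objective. Study objectives lists conservative and medical care among the options, and Primary study objectives speaks of therapy in general, not of invasive therapy. On that view the endpoint section is simply too narrow. This stands in part: including conservative patients is a legitimate aim, and a reader who inferred that a pooled mean would estimate nothing definable would go too far. It does not remove the contradiction, because the endpoint section and both visit schedules still tie the primary visit to invasive treatment alone.

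Second, pooling is never stated. Statistics speaks of t-tests in the plural and joins the groups with an alternative, so separate testing is at least as natural a reading. That is right, and the pooled figures are therefore conditional.

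Third, the conservative share may be small, since the exclusion criteria remove patients with contraindications to invasive treatment and those with inaccessible lesions. That is plausible, but no figure is given and the margin is one patient per age group.

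Fourth, the study is exploratory, with no adjustment for multiple testing. This lowers the stakes for error control. It does not allow two definitions of a primary result that has its own sample size and a 5% test.

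A reader might also infer that patients treated by surgery alone have no primary time point, because Statistics mentions only embolized patients. The documents do not support making that a point: Description of the procedures places resection after embolization, so resected patients are embolized patients. What remains is a difference in when the 6-month clock starts for them, since Follow-up names only interventional therapy while Secondary study objectives adds surgery. Aligning that takes one word.

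**Conclusion.** The protocol contradicts itself on the population and time point of its primary analysis, and does not fix whether the two treatment groups are pooled. That part rests on the text alone.

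The effect on power is conditional. A reader might infer that the 80% is lost whichever way the data are analysed. The documents do not support that: the calculation is sound for 74 evaluable pairs, and a pooled test keeps 81% if conservative patients also change by 5 with the same SD. What does hold is narrower. For the endpoint as defined, 80% requires at least 73 of 74 per age group to be invasively treated and evaluable. At assumed conservative shares of 10% to 30%, power for that endpoint is 77% to 65%. A pooled test ranges from 50% to 81% over the same shares, depending on how much conservative patients change.

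**What to change.** 1. Use one endpoint wording in Secondary study objectives, Primary Endpoint, Follow-up and Statistics: 6 months after completion of the last invasive procedure, whether embolization or surgery.
2. Make the primary test the 6-month comparison in invasively treated patients, as the endpoint section already defines it.
3. Report the 24-month change in conservative and medical patients as a separate, unpooled secondary analysis.
4. Give the expected number of invasively treated patients per age group and restate the power for it.

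This needs only changes of wording and no new data. The cost is that the stated power becomes less favourable; the re-wording does not restore it, and keeping 74 invasive patients per age group would need the larger enrolment shown above. The conservative part of the objective would also be answered only by a secondary analysis. If the sponsor wants it in the primary analysis, the Primary Endpoint section must define that endpoint and the groups must be tested separately.

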### Embolotherapy: Invasive therapy is indicated in patients with progressive symptoms according to the Schobinger classification. Historically, open surgical ligation and resection of the nidus had been considered the treatment of choice. However, embolization offers a less invasive way of treatment with lower morbidity and acceptable results. In some cases preoperative embolization is an option when complete surgical resection of the nidus is achievable thereafter.

The goal of endovascular embolotherapy is to occlude the nidus or fistulas completely. Commonly used agents are ethanol, N-butyl cyanoacrylate (NBCA) and ethylene-vinyl-alcohol-copolymer (EVOH). Additionally, coils or vascular plugs are needed in some cases, but those only occlude the feeding vessels and never reach the actual nidus, therefore the use is considered as adjuvant, mere coiling of AMVs is nowadays obsolete. Many authors use a combination of the following embolic agents for the endovascular treatment of complex fast-flow malformations.

- *Ethanol.* If injected in the right manner, ethanol is a very potent embolic agent for the occlusion of symptomatic fast-flow malformations. However, there is a high risk of tissue necrosis, nerve injury, and even cardiocirculatory arrest. Because of its low viscosity ethanol passes the nidus very quickly centrally into the lung circulation. Therefore, the pulmonary arterial pressure (PAP) should be monitored continuously during ethanol application. PAP above 25mmHg systolic can be found 10 to 15 minutes after application. To avoid side effects many interventionalists administer less than 0.5 ml per kg.
- *N-butyl cyanoacrylate (NBCA):* N-butyl cyanoacrylate (NBCA) and derivatives are liquid adhesive agents that polymerize irreversibly when exposed to blood. To adjust polymerization time and to enable fluoroscopic visibility NBCA is commonly mixed with lipiodol (ratio, 1:1 to 1:5). One major drawback of NBCA is the potential risk of catheter tip adhesion inside the lesion and the passive, flow-directed administration.

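### The primary endpoint is defined only after invasive treatment, but the primary t-tests and the sample size also take in conservatively and medically managed patients, at a different visit

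*Protocol*

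**What the plan says.** The Primary Endpoint section sets the endpoint as patient-reported "health-related Quality of Life in a multimodal therapy concept for AV malformation treatment at 6 months after completion of invasive treatment", measured with the SF-36v2 or the SF-10. The Follow-up section puts the label on one visit only: "After completion of interventional therapy follow-up is performed at 6 (primary endpoint), 12 , 24 and 36 months". The visit list under Secondary study objectives does the same and extends it to surgery. In both places the conservative schedule is six-monthly for 36 months, and none of its visits is marked as primary.

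The Statistics section describes the primary analysis as paired t-tests on four scores (PCS and MCS in adults, PHS and PSS in children). They compare baseline with the score "at 6 months after the end of treatment (for embolized patients) or at the 24 months FU (for patients with conservative or medical treatment").

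The same section sizes the study: "A sample size of N=74 (for children and adults, respectively) achieves 80% power to detect a mean of paired differences of 5", with a standard deviation of differences of 15 and a two-sided alpha of 0.05. Study population gives 148 patients in total. Neither place divides the number by treatment.

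**The concern.** The endpoint and the primary analysis do not describe the same patients. Someone managed conservatively or medically throughout never completes invasive treatment and so cannot contribute the endpoint as defined. The Statistics section still enters that person in the analysis of the primary parameters, at a visit with a different time origin and a longer interval from the start of management.

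Two things are at stake. The first is what the headline mean change means. If the groups are combined, it is a weighted average whose weights are set by the treatment mix of the centres, and it estimates neither the 6-month result after invasive treatment nor the 24-month result without it. The second is the power claim. It was worked out for 74 patients per age group, but the endpoint as defined is available only in those among them who are treated invasively.

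**Working it through.** **1. The plan's own figure.** Inputs from Statistics: mean paired difference 5, SD of differences 15, two-sided alpha 0.05, power 80%. The normal approximation is n = (15 × (1.960 + 0.842) / 5)² = 70.6, so 71. The exact calculation uses the noncentral t distribution with n − 1 degrees of freedom and noncentrality (5/15)√n. It gives 80.2% at n = 73 and 80.8% at n = 74. The stated 74 reproduces; the arithmetic is not at fault.

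**2. Who the 74 are.** 74 children + 74 adults = 148, the whole planned study. Nothing is left over for a further division by treatment.

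**3. Pooled or separate?** The sentence does not say. Three features favour pooling: one sentence covers both kinds of patient, joined by an alternative; the plural in t-tests is already explained by the four scores; and the sample size has one group per age stratum. If separate tests were meant, the two treatment groups in an age stratum must share 74 patients, so neither has 74 unless the other is empty. To detect 5/15 with 80% power in both would take 2 × 73 = 146 per age stratum, 292 in total.

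**4. Power for the endpoint as defined.** Let f be the non-invasive share. The protocol does not give it, so a range is assumed. The number available is 74(1 − f), rounded; the effect and SD are kept at 5 and 15.

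| f | invasive patients per age group | power |
|---|---|---|
| 0% | 74 | 80.8% |
| 10% | 67 | 76.7% |
| 20% | 59 | 71.2% |
| 30% | 52 | 65.5% |
| 40% | 44 | 58.0% |

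**5. What a pooled test would estimate.** Let d be the mean change at 24 months in the non-invasive patients, also not given. The pooled mean is 5(1 − f) + d·f and the pooled variance is 15² + f(1 − f)(5 − d)². For f = 30%, with n = 74 pooled:

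| d | pooled mean | pooled power | power, 52 invasive patients only |
|---|---|---|---|
| −2 | 2.90 | 36% | 65.5% |
| 0 | 3.50 | 49.9% | 65.5% |
| +2.5 | 4.25 | 66.9% | 65.5% |
| +3 | 4.40 | 70.0% | 65.5% |

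The two powers cross at a gain of roughly 2 to 2.5 points across shares of 10% to 40%. Below that, pooling costs power; above it, pooling gains power. In every row the pooled mean differs from the 5 points assumed for invasive patients.

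**The case against.** The strongest reply is that the protocol never writes that the groups are combined. It names a time point for each kind of patient, the Study design section promises a comparison of therapy approaches, and Statistics foresees summaries by study treatment. That stands as far as it goes: a reader might take pooling as fact, and the text supports it only as the likelier inference. Separate tests do not remove the problem, however. The conservative test would still lie outside the defined endpoint, and the sample size would not serve both groups. The summaries by treatment are descriptive and do not settle what the primary test is.

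A reader might also infer that pooling always loses power. It does not; the sign depends on an unknown change, as step 5 shows. The protocol's account of conservative therapy says that compression can improve quality of life, so a zero or negative change is not an obvious default.

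A third tempting step is to read "Invasive therapy is indicated in patients with progressive symptoms according to the Schobinger classification" as meaning that conservatively managed participants have no indication and so will not improve. The sentence says nothing about who is managed conservatively in this study. Treatment follows interdisciplinary consensus, and patients with contraindications to invasive treatment or an inaccessible lesion are excluded. For the same reason the non-invasive share may be small.

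Finally, the Study objectives section does cover conservative and medical therapy, and the study is exploratory. That justifies following and reporting these patients. It does not turn their 24-month score into the endpoint that the protocol defines, tests at 5% and uses for its sample size. A statistical analysis plan could add detail, but the conflict is between two statements already fixed in the protocol.

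**Conclusion.** The contradiction is real and should be resolved before analysis: the endpoint is confined to patients who complete invasive treatment, and the primary tests are not. Under the likelier, pooled reading, the tested mean does not estimate the stated endpoint. Under the separate reading, one of the tests has no matching endpoint and the sample size does not power each treatment group.

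On both readings, the 80% figure holds for the defined endpoint only if essentially all patients are treated invasively. With an assumed non-invasive share of 10% to 40%, it falls to between 76.7% and 58.0%. That range rests on the protocol's 5 and 15 applying to invasive patients, on the same share in both age groups, and on no dropout. It does not depend on how conservative patients change. No general claim is made that pooling reduces power.

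**What to change.** In Statistics, state the primary test as the paired comparison of baseline with 6 months after completion of invasive treatment, in invasively treated patients, separately for children and adults. Use the wording of the Primary Endpoint section, so that surgery is covered as well as embolization; the present sentence names embolized patients only. Report the 24-month change in conservatively or medically managed patients as a separate estimate with a 95% confidence interval, outside the primary test. Restate the power for the number of invasively treated patients expected per age group, and give the assumed share.

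The cost is a smaller n and a less favourable stated power for the primary test. No visits or patients are added. Should the sponsor wish to keep 74 invasively treated patients per age group, enrolment would have to be 74/(1 − f): 83, 93, 106 or 124 per age group at shares of 10%, 20%, 30% or 40%. That is a separate choice and is not needed to remove the contradiction.
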